## Abstract

**Background:**

Given the documented decline in levels of physical activity in early adolescence, promoting physical activity in young people is a priority for health promotion. School physical education (PE) is an important existing network in which participation in physical activity beyond school can be promoted to the captive young people. The objective of current article is to present the protocol for a PE teacher-delivered theory-based trial to promote secondary school students’ participation in physical activity out-of-school contexts. The intervention will be guided by the trans-contextual model explaining the processes by which PE teachers’ support for autonomous motivation in the classroom promotes students’ motivation to engage in out-of-school physical activity. We hypothesize that school students receiving the teacher-delivered intervention to promote autonomous motivation toward physical activity will exhibit greater participation in physical activities outside of school, relative to students receiving a control intervention.

**Methods:**

The trial will adopt a waitlist-control design with cluster-randomization by school. PE teachers assigned to the intervention condition will receive a two-week, 12-h training program comprising basic information on how to promote out-of-school physical activity and theory-based training on strategies to promote students’ autonomous motivation toward physical activity. Teachers assigned to the waitlist control condition will receive an alternative training on how to monitor physical functional capacity in children with special needs. PE teachers (*n* = 29) from eleven schools will apply the intervention program to students (*n* = 502) in PE classes for one month. Physical activity participation, the primary outcome variable, and psychological mediators from the trans-contextual model will be measured at pre-trial, post-trial, and at one-, three- and six-months post-trial. We will also assess teachers’ autonomy-supportive techniques and behaviours by observation.

**Discussion:**

The study will make a unique contribution to the literature by testing a theory-based intervention delivered by PE teachers to promote school students’ participation in out-of-school physical activity. Information will be useful for educators, community stakeholders and policy makers interested in developing programs to promote students’ out-of-school physical activity.

**Trial registration:**

ISRCTN39374060. Registered 19.7.2018.

**Electronic supplementary material:**

The online version of this article (10.1186/s12889-019-6478-x) contains supplementary material, which is available to authorized users.

## Background

### Promoting physical activity in school

Epidemiological data consistently indicate that levels of physical activity decline with age [1]. Consistent with these trends, national survey data from Finland indicate a decline in physical activity during adolescent years with only 41% of 11-year olds and 17% of 15-year olds meeting current national guidelines for physical activity [2]. Given that low levels of physical activity are related to increased risk of chronic illness later in life, and increased rates of conditions such as overweight and obesity [3, 4], the promotion of physical activity participation among young people is a public health priority. Physical education (PE) stands in an advantageous position for promoting the benefits of leisure physical activity as it addresses young, diverse and captive audiences [5]. Importantly, it is through PE that young people experience a variety of physical activities, and it is these experiences that may determine future involvement in physical activity during leisure time [6]. One of the primary aims of PE is to provide young people with the necessary motor skills, knowledge and competence to choose and participate in health-related physical activity in their leisure time [7]. Nevertheless, there is relatively little research outlining how PE teachers or PE programs can effectively orient young people toward participation in regular leisure-time physical activity outside of school.

The present article outlines the protocol of a trial in which PE teachers will be trained to support autonomous motivation toward leisure-time physical activity in lower-secondary school students (the PETALS trial). The trial aims to capitalize on school PE as an existing network to promote out-of-school physical activity in secondary school students. The trial will adopt a cluster randomized design and implement an intervention based on psychological theory to train participating teachers in techniques that support school students’ motivation to participate in physical activity in their leisure time outside of school. Trial effectiveness will be evaluated in terms of effects on participating school students’ post-intervention out-of-school physical activity participation. The theoretical basis for the intervention will be described next, followed by the study objectives.

### Theoretical basis for the intervention

The identification of factors that determine physical activity participation, and the processes by which they affect action, is paramount in providing formative evidence on which to base effective behavioural interventions [8]. The application of psychological theory, particularly theories of motivation and attitudes, has been at the forefront of providing an evidence base for the factors that drive participation in physical activity [9, 10]. However, only recently has this evidence has been applied to understand how teachers can promote students’ physical activity outside of school [10]. Such evidence is essential as it provides guidance on the content of interventions likely to be effective in promoting physical activity participation.

Self-determination theory is a prominent theory of motivation that has been applied to understand participation in health behaviours like physical activity [11, 12]. Central to the theory is the construct of self-determined or *autonomous* motivation. This form of motivation reflects an individuals’ general reflection on the causes of their action. Self-determined or autonomously-motivated individuals engage in actions such as physical activity out of interest, choice, and the sense of personal involvement they feel when engaged in the physical activities. In contrast, individuals who feel that their actions are less self-determined are likely to feel that their actions are controlled by external contingencies and engage in activities because they feel pressured, forced or obliged to do so. Research has indicated that autonomously-motivated individuals are more likely to persist with activities and more likely to gain positive or adaptive outcomes [13]. There is increasing research demonstrating that autonomous motivation is related to uptake and persistence with health behaviours [14] particularly physical activity [15, 16]. The proposed mechanism by which autonomous motivation leads to adaptive outcomes is through greater interest, effort, and involvement in the task [17].

Given that autonomous motivation has been shown to be related to persistence on adaptive behaviours, researchers and interventionists have sought to identify the contexts and conditions that promote and give rise to autonomous motivation. In particular, the focus on motivational ‘environment’ or ‘climate’ provided by the actions of significant others with leadership roles (e.g., coaches, teachers, instructors, bosses) has been shown to be influential in developing autonomous motivation. Specifically, leaders’ autonomy-supportive behaviours such as provision of choice and support for self-directed action have been shown to promote autonomous motivation and persistence in individuals operating in that environment [18, 19]. In addition, individuals’ perception that significant others in their environment are autonomy supportive have been shown to be strongly related to autonomous motivation as well as other adaptive outcomes in multiple contexts [14, 20–22]. In educational contexts, therefore, teachers can take the lead role in fostering autonomous motivation toward learning activities in the classroom by adopting autonomy supportive behaviours. Autonomy support focuses on style and delivery of lesson content rather than the content itself [23]. Interventions that have adopted autonomy support techniques and interactive styles have been found to be effective in multiple contexts in producing positive motivational and behavioural outcomes. Importantly, evidence exists that autonomy-supportive interventions can produce long-term changes in motivation and behaviour in academic settings [24, 25].

While there is considerable research demonstrating links between the use of autonomy-supportive intervention techniques and student autonomous motivation and adaptive outcomes in class, comparatively less research has focused on the role that autonomy support in educational settings has on students’ behaviour outside the class (e.g., participation in sport and physical activities during leisure time). Recent theory has proposed the potential mechanisms by which autonomy support in an educational context like PE may lead to participation in physical activities outside of school. Capitalizing on multiple theories of motivation, particularly self-determination theory [12] and the theory of planned behavior [26] the trans-contextual model (TCM) was developed [6]. The model (Fig. 1) outlines how teachers’ autonomy support for in-class activities in PE context transfers to autonomous motivation toward, and future intentions to engage in, leisure-time physical activity in an out-of-school context. According to the model, teachers’ promotion of students’ autonomous motivation toward physical activities in PE will lead individuals to strategically align their motivation, beliefs, and intentions toward similar activities in related contexts with those motives. A review and meta-analysis of studies adopting the model provided support for model predictions across multiple studies [10]. In particular, the analysis supported links between autonomy support from teachers and autonomous motivation in school, consistent with previous research [27, 28]. In addition, the research supported trans-contextual links between autonomous motivation in school and autonomous motivation, beliefs (attitudes, subjective norms, and perceived behavioural control), and intentions toward participation in physical activity outside of school, and actual participation in physical activity outside of school.

**Fig. 1 Fig1:**
[figure not shown]
Theoretical framework: Trans-contextual model

The trans-contextual model provides a theoretical framework for developing interventions in educational contexts such as school PE to promote motivation toward, and actual participation in, related activities such as physical activity outside of school. The model implies that strategies aimed at fostering autonomous motivation will promote in-school and out-of-school autonomous motivation toward physical activity, and promote adaptive beliefs and intentions toward out-of-school physical activity and actual physical activity participation. These proposed effects are supported by research demonstrating the trans-contextual effects and confirming the relevant mechanisms involved [10]. The most effective means to support autonomous motivation in school is for teachers to display autonomy-supportive behaviours during PE lessons. Consistent with the model, effects of interventions aimed at promoting autonomy support in students on out-of-school physical activity is expected to be mediated by autonomous motivation in both contexts, beliefs, and intentions. Together, these mediators provide a demonstration of how the intervention functions in promoting physical activity behaviour. In other words, it provides a framework on *how* the intervention works.

The primary focus of this study is to test the effectiveness of an intervention based on the trans-contextual model in promoting out-of-school physical activity. However, we will also control for key demographic, environmental, and psychological variables that may moderate or affect intervention effects. With respect to demographic variables, we will control for effects of student’s age, gender, nationality, ethnicity and parental education level, given the potential for these variables to affect levels of physical activity and engagement in school. With respect to environmental variables, the autonomy support offered by parents and peers towards out-of-school physical activity, parental affection, and parental control may affect students’ performance and engagement in school [29, 30] and will also be considered covariates in our analysis of intervention effectiveness. Finally, we will also control for individual difference characteristics that have been shown to affect students’ motivation in previous research. These variables include grit [31] and self-discipline [32], two factors shown to be related to long-term effort and perseverance on tasks. Finally, we will also control for the extent to which students habitually perform physical activity out-of-school. The intervention may have less effect on students who have strong exercise habits, as they are already likely to exercise regularly and are unlikely to respond to motivational messages.

### Objectives

The purpose of the current protocol article is to report the development of a school-based intervention based on the trans-contextual model to promote secondary school students’ physical activity participation by fostering autonomous motivation (the PETALS trial). The trial will adopt a cluster-randomized waitlist-control design, and participants will be teachers of lower-secondary school PE classes and their students. The intervention will involve initial training of PE teachers of lower-secondary PE classes on the use of autonomy support strategies in their regular lessons, followed by an implementation period in which teachers apply their training in regular PE classes. Effects of the intervention will be evaluated through changes in subsequent follow-up measures of participating students’ physical activity levels and trans-contextual model variables relative to pre-trial baseline measures. We will also evaluate effects of the intervention on PE teachers’ autonomy-supportive behavior measured using self-report and observation. We will also control for support for autonomy from parents and peers. Other salient demographic and individual difference variables will be also controlled for. We expect the research will provide formative evidence of an effective, replicable, low-cost behavioural intervention, which will help in developing long-term participation in physical activity in young people. In addition, key deliverables of the research will be a set of training materials and an intervention manual, which will provide step-by-step accessible instructions on how to implement the intervention and can be disseminated to schools with no specialist knowledge and minimal cost.

## Methods

### Trial design

The study will adopt a cluster-randomized, wait-list control, single-arm intervention design with randomization by school. The trial comprises two phases: a teacher-training phase and an implementation phase. The teacher-training phase will comprise a two-week, 12-h training program in which secondary school teachers will receive the autonomy-support training program developed for the present study. The teacher-training program will be preceded by the pre-trial data collection occasion during which baseline measures of primary and secondary outcome variables will be taken. The training will be delivered by experienced teacher trainers as part of the teachers’ regular in-service training. The implementation phase will comprise a one-month period during which teachers will apply their training in their regular PE classes and it is followed by post-trial data collection occurrence. Thereafter, primary and secondary outcome variables will be collected at one-, three-, and six-month follow-up data collection occasions. Teachers allocated to the waitlist control condition receive a 4-h training program in which they will be instructed on how to apply a monitoring system for physical functional capacity in children with special needs [33]. Secondary school teachers (*N* = 29) from 11 secondary schools and their students (*N* = 502) in the city of Jyväskylä in central Finland will be invited to participate in the study.

### Participants and eligibility criteria

Qualified full-time PE teachers teaching regular PE lessons in lower secondary schools will be eligible to participate in the study. Participating teachers will be asked to select one of their PE classes to be invited to participate in the study. Students in grades 7–9 (typical ages 13–15 years) in lower secondary schools will be eligible to participate. Students with existing physical or mental health condition that prevents participation in PE lessons, regular physical activity or completing surveys will be excluded. The proposed participant flow diagram through the trial is presented in Fig. 2.

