### Recruitment process and informed consent

All available lower secondary level school PE teachers in the city will participate in the teacher-training phase of the study, irrespective of their participation, as the city Education Department has accepted the teacher-training phase to be part of PE teachers’ regular in-service training. We will recruit PE teachers and their students for the study via established links with schools and with support from the Education Department. Initial contact will be made with the head teacher of the school provided with details of the study aims and methods and the commitment required by the school. Once head teacher has consented their school to participate in the study, eligible teachers from each school will be invited to participate and provided with information on the study, and the benefits and requirements of participation, and given the opportunity to ask questions. Teachers agreeing to participate to the study will complete an opt-in informed consent form. Students of the PE teachers will be recruited to the study by referral from their teacher. Invitation letters, study information, and opt-out consent forms, with the exception of opt-in consent form for participation in the accelorometry component of the study measures, will be sent to eligible students’ parents or legal guardians via the schools’ online administration and communication software or via email or post. Students whose parents or guardians decline to give consent for their child to participate in the study will be exempted, and will be provided with alternative activities while participating students complete study measures at data collection time points.

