### Randomization

The core research team will enroll PE teachers and their students to the trial. Schools (*N* = 11) consenting to participate in the trial will be randomized to the intervention or waitlist control conditions. Randomization will be conducted by a researcher independent of the core research team using a random number generator. After generation of the random allocation sequence, the researcher will seal the names of the schools and their allocation in envelopes. Recruitment of teachers and students for the intervention and wait-list control groups will be drawn from the appropriate clusters. The cluster-randomized design precludes potential for contamination of data across conditions caused by the presence of participants from different conditions within schools. The waitlist-control design ensures that the benefits of a potentially effective intervention are not withheld from control group participants.

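### Teachers select the class that enters and recruitment is described by arm after schools are randomised, so the arms can differ by class selection unless the choice precedes disclosure of allocation

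*Protocol article*

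**What the plan says.** Participants and eligibility criteria: "Participating teachers will be asked to select one of their PE classes to be invited to participate in the study". No rule governs the choice.

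Recruitment process and informed consent: the head teacher consents for the school, then "Teachers agreeing to participate to the study will complete an opt-in informed consent form". On the students: "Students of the PE teachers will be recruited to the study by referral from their teacher". Parents receive "Invitation letters, study information, and opt-out consent forms, with the exception of opt-in consent form for participation in the accelorometry component", so student entry is opt-out except for accelerometry.

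The Randomization section has four statements, in this order:
- Who enrols: "The core research team will enroll PE teachers and their students to the trial".
- What is randomised: "Schools (*N* = 11) consenting to participate in the trial will be randomized to the intervention or waitlist control conditions".
- How the allocation is concealed: "After generation of the random allocation sequence, the researcher will seal the names of the schools and their allocation in envelopes".
- How each arm is then filled: "Recruitment of teachers and students for the intervention and wait-list control groups will be drawn from the appropriate clusters".

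The time at which the envelopes are opened is not given. The Blinding section names only the researcher who randomises and the assistants who code the lesson recordings.

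Trial design puts baseline measurement before teacher training, but does not place it before or after disclosure of allocation.

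**The concern.** Randomising schools balances the schools. It balances the students measured only if they are identified independently of the arm. Here the person who delivers the intervention chooses the class, and the sentence on recruiting for each group from its own clusters follows the steps that create the allocation. The natural reading is that a teacher may know the arm when choosing.

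The Discussion anticipates teacher resistance to autonomy support and worries about classroom discipline. A teacher about to practise the techniques for a month could therefore prefer a cooperative, motivated class. Motivation is a mediator in the model and the primary outcome is self-reported activity, so a difference created by class choice would resemble the hypothesised effect. It could not be undone after recruitment.

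**Working it through.** **The plan's own figures.** No stated figure bears on class selection. The recruitment target is 286 / (1 - 0.40) = 476.7, against 476 stated, which agrees up to rounding. The fix does not change it.

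**Order of events.** Two readings fit the text.
- *Arm known at class choice.* The choice can depend on the arm, and the comparison is exposed.
- *Choice before disclosure.* Both arms choose in the same way, and only representativeness is affected.

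**Expected size under the first reading.** The documents give no class ICC, number of classes per teacher (K) or strength of selection (rho, the correlation between the teacher's basis for choosing and the class's activity level). All three are assumed. If only intervention teachers pick their apparently most active class, the expected spurious difference in SD units is

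shift = rho x sqrt(ICC) x E[max of K standard normals],

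with E[max] = 0.563, 1.03 and 1.269 for K = 2, 4 and 6 (simulated). Cells give rho = 0.3 / 0.5 / 1.0.

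| K | ICC 0.02 | ICC 0.05 | ICC 0.10 |
|---|---|---|---|
| 2 | 0.024 / 0.040 / 0.080 | 0.038 / 0.063 / 0.126 | 0.053 / 0.089 / 0.178 |
| 4 | 0.044 / 0.073 / 0.146 | 0.069 / 0.115 / 0.230 | 0.098 / 0.163 / 0.326 |
| 6 | 0.054 / 0.090 / 0.179 | 0.085 / 0.142 / 0.284 | 0.120 / 0.201 / 0.401 |

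The lowest cell is 0.3 x sqrt(0.02) x 0.563 = 0.024. The highest is 1.0 x sqrt(0.10) x 1.269 = 0.401.

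**For scale.** With 286 students in two equal arms, the difference detectable at 90% power and two-sided 5% is (1.960 + 1.282) x sqrt(4/286) = 0.38 SD, ignoring clustering. At ICC 0.05 with 286/29 = 9.9 students per class, the design effect is 1 + 8.9 x 0.05 = 1.44, and the figure becomes 0.38 x sqrt(1.44) = 0.46 SD.

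**Effect of baseline adjustment.** This was a null simulation with 11 schools (6 v 5), 29 classes, 10 analysed students per class and K = 4. It assumed school ICC 0.02 and a within-student baseline-outcome correlation of 0.5. Analysis was by linear regression on school means, with 2000 runs per cell. The class level was taken to be the same at baseline and follow-up. With only intervention teachers selecting:

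| ICC, rho | Bias, unadjusted | Type I error | Bias, adjusted | Type I error |
|---|---|---|---|---|
| 0.05, 0.5 | 0.114 | 9.2% | 0.024 | 5.2% |
| 0.05, 1.0 | 0.228 | 24.6% | 0.055 | 6.4% |
| 0.10, 0.5 | 0.158 | 12.6% | 0.027 | 4.6% |
| 0.10, 1.0 | 0.322 | 37.1% | 0.065 | 7.2% |

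When both arms select in the same way, bias is within 0.01 SD of zero and type I error is 4.8-5.8%. With no selection in either arm, which is what a random draw gives, bias is within 0.01 SD of zero and type I error is 4.3-5.7%.

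**The case against.** The strongest reply is that the article never says allocation is known when classes are chosen. The Randomization section mentions enrolment before randomisation, so its sentence order is not a strict timeline. The recruitment sentence may mean only that participants take the arm of their school, and sealing allocations suggests that concealment was intended. The flow diagram and timeline, which might show the order, are not available in the text reviewed. This stands: the post-allocation reading is an inference, and without disclosure the between-arm bias disappears.

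Other points also stand in part.
- **Motive.** A reader might infer that teachers facing 12 hours of training would choose differently from those facing 4 hours. The documents do not establish this. All available teachers in the city attend the training phase whether or not they join the study, and control teachers receive the autonomy-support programme after the three-month follow-up. The direction of any selection is unknown.
- **Referral.** A reader might take teacher referral to mean picking individual students. The text describes inviting a class and sending opt-out forms to parents. It does not describe selection within the class.
- **Existing protection.** Schools consent before randomisation, baseline precedes training, and the analysis controls for earlier values and for habit, grit, self-discipline and other covariates. These limit the bias. However, the Data analysis section adjusts for the previous time point, which at the later follow-ups is, as written, a post-allocation measure. No measured covariate reaches selection on unmeasured responsiveness.

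The reply that this is only detail left out of a condensed article does not fully answer the point. Discretionary class choice is a stated rule, and recruitment by arm is stated wording.

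**Conclusion.** The point holds in a conditional form. The stated procedure leaves differential class selection open, because the chooser is not listed as blind, recruitment is described by arm after randomisation, and the moment of disclosure is not fixed. If the arm is known at class choice, the arms can differ by selection. If it is not, the choice affects only how representative the classes are.

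The size is unknown, and every selection input is an assumption. The unadjusted range is about 0.02-0.40 SD. After baseline adjustment it is about 0.02-0.07 SD with type I error near 5-7%, for 4 classes per teacher, ICC 0.05-0.10 and selection on stable class activity. The documents do not support a claim that the trial will be biased.

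A reader might also infer that a random class draw settles the matter. It removes class-choice selection only. Allocation-driven teacher opt-in and parental opt-out are prevented by keeping allocation concealed until enrolment is complete. The change is a cheap improvement worth making, because the problem cannot be repaired after recruitment.

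**What to change.** 1. In Participants and eligibility criteria, replace teacher choice: each consenting teacher lists all eligible grade 7-9 classes, and the independent researcher draws one at random. Any redraw for scheduling reasons is also random and is made before disclosure.
2. In Recruitment process and informed consent and in Randomization, state that teacher consent, class draw and the student list are complete before the school envelopes are opened. Preferably, parental opt-out and baseline measurement are complete by then too.
3. Reword the Randomization sentence on recruiting for the two groups so that it says participants take the arm of their school and does not imply recruitment by known arm.

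Cost: up to 29 random draws by a researcher already appointed, plus the wording. The sample size does not change. The downside is less timetable flexibility and, because training follows baseline directly, shorter notice to schools of which training they will receive. The documents give no figures from which to cost that notice.
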